### Objectives and research hypotheses

This study is evaluating the behavioral and psychosocial effects of the routine offer of RGCT to newly diagnosed primary breast cancer patients who meet criteria for being at-risk of having a *BRCA1 *or *BRCA2 *gene mutation. RGCT is being offered to women shortly after diagnosis, prior to surgery. The comparison group is composed of women who receive usual care (UC), in which RGCT is available but is rarely recommended or requested.

The specific research hypotheses are:

1. A significantly greater percentage of women in the RGCT group as compared to the UC group will undergo a direct bilateral mastectomy (BLM).

2. A significantly greater percentage of women in the RGCT group as compared to the UC group will undergo a delayed prophylactic contralateral mastectomy (CPM).

3. Women in the RGCT group will report significantly lower levels of perceived cancer risk, cancer worries, and cancer-related distress at 12 month follow-up than women in the UC group.

4. Women in the RGCT will have significantly higher levels of knowledge of genetic issues in breast cancer, and higher levels of decisional satisfaction than women in the UC group.

5. Following from hypotheses 1 and 2, women in the RGCT group will report significantly more problems with body image and sexuality than those in the UC group. No significant differences will be observed between the RGCT and the UC groups on other HRQL outcomes.

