### Sample size

The sample size calculations are based primarily on the type of surgery chosen, and specifically on the uptake of bilateral mastectomy. With a total sample of 255 women (170 in the RGCT arm and 85 in the UC arm), the study will have 80% power to detect a difference of 18% versus 5% in the uptake of bilateral mastectomy, with the p-value set at 0.05. The sample size ratio of 2:1 was chosen to ensure that the RGCT sample is sufficiently large to obtain stable estimates of bilateral mastectomy and delayed prophylactic contralateral mastectomy uptake among *BRCA1/2 *carriers, and to allow for secondary analyses (e.g., to examine predictors of DNA testing uptake). The percentages indicated above are based on the following assumptions: (1) based on the participating hospitals' experiences in the previous three years, 5% of the women in the UC arm are expected to choose bilateral mastectomy; (2) in the RGCT arm, it is expected that 20% will test positive for a *BRCA1 *or *BRCA2 *mutation, of whom, on average, 50% will opt for a bilateral mastectomy. Of the remaining 80% of women in the RGCT arm, we expect a 10% uptake of bilateral mastectomy. For the remaining, primarily self-report outcomes (e.g., cancer worries and cancer-specific distress, decisional satisfaction, HRQL), the sample of 255 participants is more than sufficient to detect a 0.5 standard deviation between-group difference in mean scores. Based on data obtained from the cancer registries of the Integral Cancer Centers of Amsterdam and Middle Netherlands, and on data provided by the participating hospitals, it is estimated that there will be a total of 2550 newly diagnosed breast cancer patients during the recruitment period. Approximately 15% of these women is expected to be eligible for participation. Based on prior experience with recruitment of patients into similar studies, we expect an 80% response rate. This results in an expected N of 306 patients. This allows for an attrition rate of 17%, while retaining 255 women for the primary analysis.

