### Statistical analyses

Analyses will first be performed to evaluate the comparability of the RGCT and the UC groups at study entry in terms of sociodemographic and clinical characteristics. Student's t-test or appropriate non-parametric statistics will be used, depending on the level of measurement. If the groups are not comparable on one or more background variables, those variables will be employed routinely as covariates in subsequent analyses. Between group differences in choice of surgery will be tested using the chi-square statistic or, if statistical adjustment is required for covariates, multiple logistic regression analysis. Analysis of (co)variance will be employed to assess group differences at 6 and 12 month follow-up in risk perception, psychological distress, knowledge, decisional satisfaction, and HRQL. Where appropriate, sociodemographic and clinical background variables, as well as baseline scores on the outcomes of interest, will be used as covariates. Effect sizes will be calculated using standard statistical procedures. Supplementary, descriptive analyses (both quantitative and qualitative) will be used for reporting the patients' experiences with RGCT. All primary analyses will, to as great an extent as possible, be conducted on an intention-to-treat basis. That is, all women in the RGCT group will be included in that group in the analyses, regardless of whether they actually carried through with RGCT. Supplementary analyses will be undertaken to examine sociodemographic, clinical and psychosocial factors associated significantly with (non-) attendance at the RGCT and uptake of BLM.

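### Hypothesis 5 predicts no significant difference on the other HRQL outcomes, and the planned difference-type ANCOVA cannot confirm that prediction

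*Protocol article*

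**What the plan says.** Hypothesis 5 (Protocol article, Objectives and research hypotheses) has two parts. The first predicts harm on two domains: "women in the RGCT group will report significantly more problems with body image and sexuality than those in the UC group". The second makes a no-difference prediction for the rest: "No significant differences will be observed between the RGCT and the UC groups on other HRQL outcomes".

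The Statistical analyses section gives one method for HRQL, an analysis of (co)variance "employed to assess group differences at 6 and 12 month follow-up in risk perception, psychological distress, knowledge, decisional satisfaction, and HRQL". Where appropriate, background variables "as well as baseline scores on the outcomes of interest, will be used as covariates". It adds: "Effect sizes will be calculated using standard statistical procedures". Primary analyses are by intention to treat as far as possible.

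The Sample size section plans 170 women in the RGCT arm and 85 in the UC arm, retained after attrition. For the self-report outcomes it says only that 255 women are "more than sufficient to detect a 0.5 standard deviation between-group difference in mean scores". The article gives no equivalence or non-inferiority margin and no confidence interval criterion.

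**The concern.** As worded, the second part of hypothesis 5 is fulfilled when the tests come out non-significant. That outcome arises when the arms are alike, but also when they differ by an amount that the trial is too small or too noisy to show. The planned test can count against the prediction; it cannot establish it.

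The wording is also fragile the other way. HRQL is measured on many scales at two time points, and the article does not say how isolated significant results bear on a prediction of none.

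At stake is what the trial may say about general quality of life after an early offer of genetic counseling and testing. The psychosocial effect of RGCT is part of the study's stated aim, so this conclusion should rest on a criterion that the data can meet or fail.

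**Working it through.** **Inputs.** From the Sample size section: 170 and 85 women analysed, a p-value threshold of 0.05, and 0.5 SD as the difference named for self-report outcomes. From Study measures: the QLQ-C30 has 5 functional and 3 symptom scales, besides single items and the QLQ-BR23. Assumed: two-sided testing, equal SDs, normal approximation, and no gain from baseline adjustment unless stated.

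**1. The plan's own statement on 0.5 SD.**
- SE = √(1/170 + 1/85) = 0.1328 SD.
- Power at 0.5 SD = Φ(0.5/0.1328 − 1.96) = Φ(1.80) = 96.4%.
- For 80% power, 48 UC women (144 in all at 2:1) would be enough.

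The claim that 255 is more than sufficient for 0.5 SD is therefore confirmed.

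**2. Precision.**
- 95% CI half-width = 1.96 × 0.1328 = 0.260 SD.
- Smallest difference detectable with 80% power = (1.96 + 0.8416) × 0.1328 = 0.372 SD.

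**3. Chance of a non-significant result when a true difference d exists.** This is Φ(1.96 − d/SE) − Φ(−1.96 − d/SE); the second term is negligible here.

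| True difference | d/SE | P(non-significant) |
|---|---|---|
| 0.20 SD | 1.506 | 67.5% |
| 0.25 SD | 1.882 | 53.1% |
| 0.30 SD | 2.258 | 38.3% |
| 0.40 SD | 3.011 | 14.7% |
| 0.50 SD | 3.764 | 3.6% |

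**4. The opposite error.** Take only the 8 multi-item QLQ-C30 scales, tested at 0.05 with no true differences and treated as independent. The chance of at least one significant result is 1 − 0.95⁸ = 34% at one time point and 1 − 0.95¹⁶ = 56% over two. Positive correlation between scales and visits would lower these figures.

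**5. Would 0.5 SD serve as an equivalence margin?** In two one-sided tests at 5%, the 90% CI must lie within the margin.
- The rule is met when |observed difference| < 0.5 − 1.645 × 0.1328 = 0.281 SD.
- p>0.05 requires |observed difference| < 0.260 SD.
- So every non-significant result would also pass the equivalence rule; its 90% CI could reach at most 0.260 + 0.219 = 0.479 SD.
- With a true difference of 0.25 SD, the rule is met about 59% of the time, against 53% for p>0.05. At 0.30 SD the figures are 44% and 38%.

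At this sample size a 0.5 SD margin is slightly more lenient than the criterion it would replace. The overlap is complete while 1.96 SE + 1.645 SE < 0.5 SD, which holds down to about 234 women analysed at 2:1.

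**6. What the trial could show with other margins.** The documents give none, so a range is assumed. Equivalence power at a true difference of 0 is 2Φ(margin/SE − 1.645) − 1, set to 0 where negative.

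| Assumed margin | Power, N = 255 | Same, baseline correlation 0.5 (assumed) |
|---|---|---|
| 0.2 SD | 0% | 8% |
| 0.3 SD | 46% | 66% |
| 0.4 SD | 83% | 93% |
| 0.5 SD | 97% | 99% |

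The last column multiplies the SE by √(1 − 0.5²) = 0.866.

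**The case against.** The strongest reply is that this is a wording point on a secondary outcome. Effect sizes are planned, so readers will see more than p-values. Power is about 96% for the one difference the article names, so a difference of that size would rarely be missed. The article is condensed, and interval criteria and scale-level rules are commonly left to an analysis plan that is not shown.

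Much of this is fair. The planned effect sizes are a real mitigation, although nothing makes them the basis for judging hypothesis 5. The power figure is right, but it says little about differences of 0.2 to 0.3 SD. The appeal to an analysis plan carries less weight: the article has already fixed a criterion, and a later plan could repair it only by changing what hypothesis 5 says.

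A reader might infer that non-significance will be presented as proof that RGCT does not harm quality of life. The documents do not support that. No section says how a non-significant result will be reported, and the same hypothesis predicts more problems with body image and sexuality. Nor does the article say that one significant scale would refute the hypothesis; the multiplicity figures show only how likely such a result is by chance.

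A reader might also want a sensitivity analysis restricted to women who attended RGCT, on the ground that non-attendance dilutes differences. The study evaluates the routine offer of RGCT by intention to treat, so non-attendance is part of the effect in question. Comparing a self-selected subset with all UC women would lose the randomized comparison.

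**Conclusion.** The concern stands in a limited form. The second sentence of hypothesis 5 makes non-significance its criterion, and the planned ANCOVA cannot turn non-significance into support for no difference. At the planned numbers, true differences of 0.25 and 0.30 SD would go undetected about 53% and 38% of the time, while differences near 0.5 SD would rarely be missed.

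These figures assume 255 women analysed, two-sided 5% tests, equal SDs and no baseline adjustment. A baseline correlation of 0.5 would reduce the 95% half-width to 1.96 × 0.1328 × 0.866 = 0.225 SD. If 255 were instead the number randomized and 17% were lost, it would widen to about 0.286 SD. Neither changes the conclusion.

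The point concerns only the HRQL outcomes other than body image and sexuality. The primary comparison of surgical uptake is unaffected. The change should be made because the criterion is wrong and cheap to correct.

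**What to change.** Reword the second sentence of hypothesis 5 as estimation. For every HRQL scale, report the adjusted RGCT minus UC difference with its 95% confidence interval at 6 and 12 months in the intention-to-treat population. State that p>0.05 alone will not be read as evidence of no difference.

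If the sponsor wants to be able to conclude that there is no relevant difference, it should justify and pre-specify a margin for the difference between arms, and require the 90% confidence interval of the adjusted difference to lie within it. The 0.5 SD in the Sample size section should not be adopted by default, because it is described there as a detectable difference and at N = 255 would accept every non-significant result. The choice has consequences for power: about 97% with 0.5 SD, 83% with 0.4 SD and 46% with 0.3 SD, when the true difference is 0.

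The cost is wording. The planned models already give the intervals, and no extra patients or data are needed. The downside is that some scales will be inconclusive, and the report will have to say so.

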## Methods/Design

This is a multicenter, randomized, controlled trial in which patients are randomized to RGCT or to UC on a 2:1 basis. The primary clinical outcomes include: the uptake of direct BLM or of delayed CPM. Data on surgical outcomes will be abstracted from the medical records. This protocol follows the CONSORT guidelines [34].

Psychosocial outcomes include: perceived risk for ipsilateral and contralateral breast cancer and for ovarian cancer, cancer-related worry and distress; knowledge of genetic aspects of breast cancer; decisional satisfaction; and HRQL. The study also is evaluating women's experience of and satisfaction with RGCT (i.e., the timing and quality of the services provided, the perceived impact on treatment decisions, the perceived need for additional psychosocial support, etc.), and the surgeons' experience with RGCT. Standardized questionnaires are administered at study entry (prior to randomization), and at 6 month and 12 month follow-up (see figure 1). The institutional review boards of all participating hospitals have approved the study. The study is registered at the Netherlands Trial Register (NTR1493) and ClinicalTrials.gov (NCT00783822).

**Figure 1 F1:**
[figure not shown]
**Study flow diagram**.

### Participants

The study sample will be composed of 255 women with a clinically confirmed, newly diagnosed primary breast cancer or ductal carcinoma in situ (DCIS) who meet at least one of the criteria for referral for genetic counseling and DNA analysis according to the Dutch Institute for Healthcare Improvement (CBO). These criteria are: (1) age at time of breast cancer diagnosis less than 35 years; (2) previous history of cancer in the contralateral breast, with the first breast cancer diagnosis at less than 50 years of age; (3) previous personal history of ovarian cancer; (4) a family history of ovarian cancer; (5) a first degree male relative with breast cancer; (6) breast cancer diagnosed under the age of 50 years, with a first degree relative diagnosed with breast cancer under the age of 50 years; (7) breast cancer diagnosed under the age of 50 years, with a relative with prostate cancer diagnosed under the age of 60 years; (8) breast cancer, with two or more relatives from the same side of the family diagnosed with breast cancer, where at least one family member (either the patient or a relative) was diagnosed under the age of 50 years; or (9) a proven *BRCA1/2 *mutation in the family. Women who meet one or more of these criteria are considered to have a 10% or greater chance of having a BRCA1/2 gene mutation [35,36]. Women are excluded from the study if they are younger than 18 years of age, lack basic fluency in the Dutch language, are incapable of understanding informed consent, or are diagnosed with a breast cancer recurrence or with metastastic disease. The patients are being recruited from 12 hospitals in the Amsterdam and Utrecht regions of the Netherlands.

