### Recruitment and randomization

Patient recruitment began in November 2008, following approval by the ethical review committees of the participating hospitals. Participating surgeons make use of an 11-item checklist to determine patient eligibility. All patients who meet the study inclusion criteria are informed by the surgeon or nurse practitioner about the study, and are given an envelope containing an information letter, a consent form and the baseline questionnaire. Eligible patients receive a phone call by a member of the research team within a few days, in order to carry out the informed consent procedures and to administer the baseline questionnaire to consenting patients. Patients are then randomized to the RGCT or the UC group in a 2:1 ratio. The computerized randomization is stratified per hospital and blocked per 9 cases [37]. These 12 random allocation sequences are generated by an independent individual, are stored in computer files, and remain unknown to the researchers until the patient is randomized. The participant as well as the treating surgeon or nurse practitioner is informed about the randomization outcome. The researchers are blinded to randomization outcome at the time of the baseline assessments, but not at the follow-up assessments. This is due to the fact that the researchers are responsible for arranging appointments with the genetic counselor for those women assigned to the RGCT arm of the study.

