### Intervention

Women in the RGCT group receive an appointment with a clinical geneticist or genetic counselor within one week following randomization, either at the Family Cancer Clinic of the Netherlands Cancer Institute/Antoni van Leeuwenhoek Hospital or at the Department of Medical Genetics of the University Medical Centre Utrecht. Those patients who decline to undergo RGCT are given the opportunity to receive genetic counseling and testing at a later time.

While the standard steps involved in genetic counseling are followed, the process is accelerated when necessary. All patients are asked to complete a standard, detailed family history form in order to draw a three-generation pedigree. Where possible, confirmation of the (age at) diagnosis of the affected family members is confirmed via medical record audits following required informed consent procedures. At the time of the first consultation with the clinical geneticist, the urgency of the steps to be taken are discussed and a decision about DNA testing is made. If the patient agrees, a blood sample for testing for mutations in the *BRCA1 *and *BRCA2 *genes can be taken on the same day. For women whose test result will not be of immediate consequence for their choice of treatment, the timing of the DNA testing does not need to be accelerated (i.e., DNA test results will be made available within 4 months). Examples are women who, from a medical point of view, cannot opt for breast conserving therapy and have already had a contralateral mastectomy, women who do not wish to take immediate secondary preventive measures, or women whose family history provides them with sufficient reasons to undergo bilateral treatment regardless of whether a mutation can be found.

Where it is anticipated that the DNA test results could influence treatment decisions, a fast-track procedure is used and the results are made available within 3 to 6 weeks. From a medical point of view, this timeframe is sufficiently short to inform patients and clinicians about the results before definite treatment decisions have to be made.

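### Some eligible women have no contralateral breast and cannot have the primary surgical outcome, yet the primary comparison counts them; the estimate is diluted and their coding is undefined, though the power loss is modest

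*Protocol article*

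**What the plan says.** **Eligibility.** The Participants section lists nine alternative routes into the trial. One is "2) previous history of cancer in the contralateral breast, with the first breast cancer diagnosis at less than 50 years of age". The exclusions concern age, language, capacity to consent, recurrence and metastatic disease. Earlier removal of the contralateral breast is not among them.

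**Such women are foreseen.** Among the examples of RGCT women whose test result has no immediate consequence for treatment, the Intervention section names those who "cannot opt for breast conserving therapy and have already had a contralateral mastectomy".

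**Primary outcome.** Methods/Design states: "The primary clinical outcomes include: the uptake of direct BLM or of delayed CPM". The Choice of surgical procedure section takes the definitive surgical treatment from the medical record.

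**Analysis.** The Statistical analyses section compares choice of surgery by chi-square (logistic regression if covariates are needed), by intention to treat as far as possible. It sets no condition that a woman must be able to have the outcome.

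**Sample size.** The plan puts 170 women in RGCT and 85 in usual care and works at a significance level of 0.05. On that footing it claims that "the study will have 80% power to detect a difference of 18% versus 5% in the uptake of bilateral mastectomy". The RGCT rate is built from uptake figures applied to the whole arm.

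**The concern.** A direct BLM and a delayed CPM both require a contralateral breast. A woman who has lost it cannot contribute an event in either arm, whatever counselling or testing she is offered. Counting her answers a slightly different question from the one in hypotheses 1 and 2.

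The effect depends on how her surgery is scored, and the article does not say.

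- **Scored as a non-event**, she lowers the observed uptake in both arms and so shrinks the absolute difference.
- **Scored as bilateral** because a one-sided mastectomy now leaves her without either breast, she adds an event that is not uptake of contralateral removal. The Background says that carriers may choose mastectomy over lumpectomy. If RGCT shifts that choice for the remaining breast, the shift could be recorded as an effect on bilateral mastectomy.

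**Working it through.** **Inputs from the Sample size section.** 170 RGCT and 85 usual care (UC); 18% versus 5%; alpha 0.05. Sidedness is not stated; two-sided is assumed because it reproduces the plan.

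**Step 1: reproduce the plan.**

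- RGCT rate: 0.20 × 0.50 + 0.80 × 0.10 = 0.18.
- Pooled rate: (85 × 0.05 + 170 × 0.18)/255 = 0.1367.
- Null standard error: √[0.1367 × 0.8633 × (1/85 + 1/170)] = 0.0456.
- Standard error under the alternative: √(0.05 × 0.95/85 + 0.18 × 0.82/170) = 0.0378.
- Continuity correction: ½ × (1/85 + 1/170) = 0.0088.
- Power: Φ[(0.13 − 0.0088 − 1.96 × 0.0456)/0.0378] = 0.80, as stated. The corrected sample-size formula gives 258, close to 255.
- Without the correction the same approximation gives 0.859. Exact enumeration of the uncorrected chi-square gives 0.874.

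**Step 2: score the affected women as non-events.** Let f be their share, equal in both arms by randomisation. The documents give no value for f, so the range is assumed. The 18% and 5% are taken to apply to women who can have the event. Both rates are multiplied by (1 − f), so the difference is 13 × (1 − f) points and the ratio stays at 18/5 = 3.6.

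| f (assumed) | RGCT vs UC | Difference | Power, corrected | Power, exact chi-square |
|---|---|---|---|---|
| 0 | 18% vs 5% | 13.0 | 80.0% | 87.4% |
| 5% | 17.1% vs 4.75% | 12.35 | 76.9% | 85.2% |
| 10% | 16.2% vs 4.5% | 11.7 | 73.5% | 82.6% |
| 15% | 15.3% vs 4.25% | 11.05 | 69.8% | 79.6% |

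**Step 3: restrict to women with a contralateral breast within the same 255.** The difference returns to 13 points, but the arms shrink by the factor (1 − f). Uncorrected approximate power moves from 83.5% to 83.8% at f = 5%, and from 80.8% to 81.5% at f = 10%. With the continuity correction the gain is also below one point.

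**Step 4: score removal of the sole remaining breast as bilateral.** Let g be the proportion of the affected women so scored. Each arm's rate becomes p × (1 − f) + f × g. With g = 60% in both arms (assumed):

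- f = 5%: 20.1% vs 7.75%, ratio 2.6, corrected power 67.6%.
- f = 10%: 22.2% vs 10.5%, ratio 2.1, corrected power 56.5%.

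With g equal in both arms the difference is still 13 × (1 − f), as in step 2, but the ratio falls and the variance rises. If g differs between arms, a term f × (g in RGCT − g in UC) is added to the difference, and it has nothing to do with contralateral surgery.

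**The case against.** The opposing case is strong on size and on the remedy.

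- **The share is unknown and may be small.** The criterion is one of nine, and it also covers women whose earlier cancer was treated with breast conservation. They can still have the outcome. This stands, so every magnitude above is conditional on f.
- **A reader might infer that the primary test is invalid or biased.** The documents do not support this. Randomisation spreads these women over both arms. As non-events they leave the type I error and the expected rate ratio unchanged.
- **The dilution may be partly counted already.** The 5% UC rate comes from the hospitals' own recent experience, which may include such women. If so, step 2 overstates the loss.
- **The named test is the chi-square, with no continuity correction mentioned.** Its exact power stays near 80% even at f = 15%. This stands.
- **Miscoding is not shown.** A reader might infer that these women will be scored as bilateral. Nothing in the article says so, detailed coding rules may sit in documents not shown, and surgical history is collected. Step 4 shows only what depends on the rule.
- **Inclusion fits the aim.** The trial studies the routine offer of RGCT to a referral population, and hypotheses 3 to 5 apply to these women too. The no-consequence example also requires that breast conservation be impossible; others still face a choice for the remaining breast. This argues against excluding them from the trial. It does not make a BLM or CPM possible for them.

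**Conclusion.** The point holds in a limited form. Read together, the eligibility criteria, the Intervention example, the outcome definition and the analysis set put women in the primary denominator who cannot have the primary outcome.

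Scored as non-events, they reduce the absolute difference in proportion to their share: 0.65 points at 5% and 1.3 points at 10%. Corrected power drops by about 3 and 6.5 points, and exact chi-square power by about 2 and 5. These figures assume the stated share, equal shares in the arms, and planning rates that refer to women with a contralateral breast.

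The gain from changing the plan is an undiluted estimate with one clear meaning. It is not a rescue of power. The larger distortion in step 4 is possible but assumed.

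**What to change.** 1. Leave eligibility and the psychosocial analyses as they are.
2. Make the primary surgical comparison among women with a contralateral breast at randomisation, by arm as randomised. The treatment history listed under Sociodemographic and clinical data identifies them. The status is fixed before randomisation, so the restriction does not select by arm.
3. State that mastectomy of a sole remaining breast does not count as BLM or CPM.
4. Report the all-randomised comparison alongside, with the number of affected women per arm.

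**Cost.** A short addition to the analysis-set and outcome definitions, and a slightly smaller primary set: about 242 women at an assumed 5% share (255 × 0.95) or about 230 at 10% (255 × 0.90). The gap between 306 expected and 255 needed does not cover this, because the plan already uses it for 17% attrition (1 − 255/306 = 0.167).
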